**Low Dose Pioglitazone Proposal**

| 1. ***Study title:*** *Safety and Efficacy of Low Dose Pioglitazone Compared with Standard Dose Pioglitazone in Type 2 Diabetes with Chronic Kidney Disease: a Randomized Controlled Trial* |
| --- |
|  |
| ***2. The purpose and rationale for the study*** |
| Throughout the world, chronic kidney disease (CKD) is a growing health concern because of its increasing prevalence and incidence rates and dismal outcomes. Despite technical advances in dialysis and transplantation, the prognosis of kidney failure remains poor. The U.S. Renal Data System provides statistics on individuals with end-stage renal disease (ESRD), which include individuals with kidney failure who are receiving dialysis, as well as kidney transplant recipients at all stages of CKD. This U.S. registry reported more than 76,500 deaths in patients with ESRD in 2001, an annual mortality rate in excess of 20% ^1^. By 2010, there will be a projected 160,000 new dialysis-dependent patients/year, double the current rate ^2^. The average life span of a patient entering a long-term dialysis program is 20-25 years less than that of the normal age-sex-race-matched U.S. population over the age of 45 ^3^. Among many factors, including treatment characteristics and co-morbid conditions, protein and calorie malnutrition has been shown to be a major risk factor for increased mortality in the ESRD patient population.^4^  Type 2 diabetes mellitus (T2DM) is one of the most important health problems and its disease prevalence has been increasing steadily all over the world. Similarly, the rising incidence of the chronic kidney disease (CKD) creates major problems for both healthcare systems and economies in future years ^5^. T2DM is often associated with CKD, and for 30 to 50% of patients receiving dialysis therapy, diabetes is the primary cause of end stage renal disease (ESRD)^6,7^. Identification and diagnosis of CKD is important to optimize clinical management recommendations for this complex patient population.  Therapeutic options for patients with T2DM and CKD are limited because the reduced glomerular filtration rate (GFR) results in an accumulation of certain drugs potentially leading to adverse side effects ^8^. Currently, thiazolidinediones (TZDs), synthetic exogenous agonists of the nuclear peroxisome proliferator-activated receptor-gamma (PPARγ), increase insulin sensitivity and inhibit adipose tissue lipolysis as well as possess anti-inflammatory and other beneficial vascular effects ^9^. TZDs undergo hepatic metabolism and has been demonstrated to be effective without increasing the risk of hypoglycemic episodes among patients with CKD ^10^. The pharmacokinetic profile of TZDS, is similar among subjects with normal or impaired renal function, remaining unaffected even by hemodialysis ^11^. Therefore, dosing of TZDs is not a required adjustment among patients with CKD.  Unfortunately, fluid retention and edema have emerged as the most common and serious side effects of TZDs and have become the most frequent cause of discontinued therapy ^12,13^. The mechanism through which TZDs induces fluid retention results from an increase in tubular sodium and water reabsorption in the collecting tubule and an increase in vascular permeability growth factors ^14^. Currently, using pioglitazone 15 to 45 mg daily is recommended for patients with T2DM. Patients with CKD might constitute a high risk population of TZDs related to fluid retention. Reducing fluid retention with low dose medications is important among those with CKD to continue the beneficial effects to optimize glycemic treatment without affecting the renin-angiotensin-aldosterone system and natriuretic peptides^15,16^. |
|  |
| ***3. The objective(s) and endpoint(s), if different from the objective(s)*** |
| - To evaluate the effects of low-dose pioglitazone (7.5 mg/day) on glucose metabolism compared with a standard-dose of pioglitazone (15.0 mg/day) among Thai patients with T2DM with CKD. - To determine side effects related to weight gain and fluid retention and the incidence of edema of low-dose pioglitazone (7.5 mg/day) compared with a standard-dose of pioglitazone (15.0 mg/day) among Thai patients with T2DM with CKD. |
|  |
| ***4. The study design*** |
| **A randomized, open-label controlled clinical trial.**  **Method**   1. The study will be started after the institute review board approval, Royal Army Medical Department. 2. Electronic case record form will be designed with subject code that personal subject’s data is not identified. 3. Patient screening will be conducted according to inclusion criteria and exclusion criteria. 4. Subjects will be divided into 2 groups (low and standard dose pioglitazone) by block randomization. The randomization and drug dispensing will be done by the investigator. The inform consent form will be read by the research staffs to the subjects and will be signed by every participated subjects. 5. The intervention group will receive pioglitazone 7.5 mg, 1 tablet 30 minutes before meal, once a day in the morning and the control group will receive the pioglitazone 15 mg as prior to the study. A recommendation card with detail of side effect and drug interaction will be provided to each subject who receives pioglitazone. 6. Five mL of blood will be collected along with 2 urine containers (at least 2 mL of urine per container) prior to the first treatment for the following items: CBC, fasting blood glucose, serum albumin, HbA1C, lipid profiles, BUN, creatinine, electrolyte, and liver function test. Body composition was assessed immediately after dialysis. Dual energy x-ray absorptiometry (DEXA) scan will be used to measure lean body mass and fat mass in grams using a whole-body scan. 7. At week 4, 8, 12, 16, 20, 24 visit, the investigator does the physical examination, symptom and drug adverse event interview, and laboratory testing such as CBC, fasting blood glucose, serum albumin, HbA1C, lipid profiles, BUN, creatinine, electrolyte, and liver function test. DEXA scan will be repeated. Contact can be made to the investigator for 24 hours regarding to any abnormal event occurs. |
|  |
| ***5. Treatment information, if applicable (e.g. for each study treatment, the dose, form, route, frequency, and duration, and if there is a dose-escalation, the dosing schema and rationale for the starting dose).*** |
| The intervention group will receive pioglitazone 7.5 mg, 1 tablet 30 minutes before meal, once a day in the morning and the control group will receive pioglitazone 15 mg as prior to the study. |
|  |
| ***6. Key milestones and estimated timelines.*** |
| **- STUDY PERIOD: 24 weeks/subject, approximately 1 year for data collection**  **-STUDY FINAL REPORT: January 2014, and December 2015 for study presentation and writing report** |
|  |
| ***7. The Investigator-Sponsor’s name, mailing address, phone number, and any other necessary contact information (e.g. email address, fax number, or both).*** |
| **Primary Investigator:** [name]  **Affiliation:** Division of Nephrology, Department of Medicine, Phramongkutklao Hospital and College of Medicine  **Address:** [name], Division of Nephrology, Department of Medicine, Phramongkutklao Hospital and College of Medicine, Bangkok, Thailand, 10400  **[contact]  **[contact]  **Email:** [[contact]](mailto:[contact])  **Co-investigator(s): [name].**  **Affiliation:** Division of Nephrology, Department of Medicine, Phramongkutklao Hospital and College of Medicine  **Address:** [name], Division of Nephrology, Department of Medicine, Phramongkutklao Hospital and College of Medicine, Bangkok, Thailand, 10400  **[contact]  **[contact]  **Email:** [[contact]](mailto:[contact]) |
|  |
| ***8. Any currently known location(s) where the study is to be conducted, including the name and full address of the institution(s) that are to be used in the study* *(including country)*** |
| Department of Medicine, Phramongkutklao hospital  [name], Phramongkutklao Hospital and College of Medicine, Bangkok, Thailand, 10400 |
|  |
| ***9. Methodology for data collection, including safety information*** |
| Electronic case record form will be designed with subject code that personal subject’s data is not identified. |
|  |
| ***10. Details of the proposed study population (including number of subjects, subject demographics [e.g. age, sex, and other key characteristics], and other key eligibility criteria).*** |
| **Expected number of subjects: 74 subjects**  **Inclusion criteria**   1. Age 18 years or older 2. Diagnosed T2DM with stable glycemic treatment with HbA1c>8% at least 12 weeks and diagnosed CKD according to [Kidney Disease: Improving Global Outcomes](https://www.google.co.th/url?sa=t&rct=j&q=&esrc=s&source=web&cd=8&cad=rja&uact=8&ved=0ahUKEwid7tCq8rPLAhVDBY4KHaXbAs8QFggyMAc&url=https%3A%2F%2Fwww.guideline.gov%2Fbrowse%2Fby-organization.aspx%3Forgid%3D2349&usg=AFQjCNFB0TRXT4TlgKTcrEguhdpN6NSZxg) (KDIGO) 2012 definition 3. No history of treatment with TZDs within 12 weeks before starting the study 4. Normal liver function, which referred to AST less than 105 U/L and ALT less than 120 U/L 5. Subject with signed consent form.   **Exclusion criteria**   1. Active malignancy 2. Severe heart, lung or liver disease, stroke, chronic infection, e.g., tuberculosis within one year of starting the study 3. Limited life expectancy within 12 months, edematous state from any cause 4. Specific contra-indications to pioglitazone including increased serum levels of liver enzyme (aspartate aminotransferase [AST] or alanine aminotransferase [ALT] >2.5 times the upper limit of normal), and history of bladder malignancy. 5. Subject without signed consent form   **Withdrawal or termination criteria**   1. The occurrence of heart failure or volume overload after drug administration which resulted in treatment needed or consent form withdrawal. 2. The occurrence of side effect which resulted in consent form withdrawal such as dizziness that affect driving, diarrhea that affect routine life. 3. The occurrence of severe infection, cardiac arrhythmia, myocardial infarction and cardiovascular hospitalization.   **Subject allocation**  Block randomization divides subjects into low dose group and standard dose group equally. A randomization in each group is conducted by dividing each subgroup into 20 groups with the setting number 0-19. The even number group, classified as A, is the intervention group. And the odd number group, classified as B, is the control group. |
|  |
| ***11. Key study assessments and procedures*** |
| The level of glycemic control is monitored by hemoglobinA1C and fasting plasma glucose.  Direct segmental multifrequency bioelectrical impedance analysis (DSM-BIA) is performed using the In-Body (720) body composition analyzer. This equipment has been shown to have high test-pretest reliability and accuracy.^17^ The spectrum of electrical frequencies is used to predict body composition, total fat mass, intracellular water (ICW) and extracellular water (ECW) compartments of the total body water (TBW) in the various body segments. |
|  |
| ***12. Statistical justification for the study design, including sample size calculations, and analysis plan.*** |
| The sample size was determined by using change in body fluid as the primary outcome measure and by extrapolating expected changes and standard deviation from data in the study of the effect of pioglitazone in T2DM patients. The target sample size was 37 subjects per group that will provide 80% power to detect a significant effect, using a 2-sided, *p*=0.05. **Formula:**  **Value description**  ** = 0.05 (two-tail)  = 1.96**  ** = 0.20  = 0.84**  **[figure not shown]**  **n = **  **[figure not shown]**  By the calculation, the quantity of subject per group is 37. But with the follow up, the 10% loss follow up of the calculated number is considered. Therefore, the quantity of subject per group is 40, total is 80.  Statistical analyses were performed using the Statistical Package for Social Sciences (SPSS) software version 11.5. Intention-to-treat analysis was used by replacing the missing data with series mean for each group. Both descriptive and inferential statistics were determined. A bi-directional α-level of significance was set at *p*= 0.05 for all measures.   - Descriptive statisticsa was used for demographic results which are expressed as mean (± standard deviation; SD) and percentage unless otherwise indicated. - Chi-square tests were used for evaluating categorical variables. - Continuous variables between study and control groups were compared with unpaired *t-*tests. - Continuous variables between baseline and at the end of study for each group of patients were compared by using paired student *t-* tests. - Analysis of covariance (ANCOVA) was used for controlling covariate factors if baseline data are different between the patient groups. - One-way repeated analysis of variance (ANOVA) was used to examine the main effects of time when comparing data obtained at one time to data obtained at another time during the study period. - One-way repeated analysis of variance (ANOVA) with between-subjects factor was used to determine the main effects of overall difference between the control and the study groups with respect to the mean of the data. |
|  |
| ***13. Details of any clinical safety reporting processes and when applicable, specific risk management interventions to safeguard subjects*** |

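### Glycaemia is an unsized, unranked objective, and neither the planned between-arm nor within-arm tests can show that the lower dose keeps its glycaemic effect

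*Protocol*

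**What the plan says.** **Objectives (Protocol, Section 3).** There are two bullets, and neither is labelled primary or secondary. The first is "To evaluate the effects of low-dose pioglitazone (7.5 mg/day) on glucose metabolism compared with a standard-dose of pioglitazone (15.0 mg/day"). The second is "To determine side effects related to weight gain and fluid retention and the incidence of edema of low-dose pioglitazone (7.5 mg/day"), against the same 15 mg comparator.

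**Rationale (Section 2).** Fluid retention is to be reduced with low-dose medication in patients with CKD "to continue the beneficial effects to optimize glycemic treatment". The study title names both safety and efficacy.

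**Primary outcome and size (Section 12).** "The sample size was determined by using change in body fluid as the primary outcome measure". "The target sample size was 37 subjects per group that will provide 80% power to detect a significant effect, using a 2-sided" 0.05 level. No other outcome is sized.

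**Glycaemic measures (Section 11).** HbA1c and fasting plasma glucose are used to monitor control. No hypothesis or margin is attached to them.

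**Analysis (Section 12).** Continuous variables are compared between arms by unpaired t-test. For change over time within an arm: "Continuous variables between baseline and at the end of study for each group of patients were compared by using paired student" t-tests. ANCOVA is used if the arms differ at baseline. Repeated-measures ANOVA is planned with and without a between-subjects factor. All measures are tested two-sided at 0.05.

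**Entry (Section 10).** "Diagnosed T2DM with stable glycemic treatment with HbA1c>8% at least 12 weeks". Both arms receive pioglitazone; there is no placebo arm.

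**The concern.** The case for a lower dose rests on two things: less fluid retention, and glycaemic benefit that is kept. Section 12 sizes the trial for the first. For the second it supplies two kinds of test, and neither answers the question.

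- A between-arm test of difference asks whether the arms can be told apart. Failing to separate them is not evidence that they are alike, least of all in a trial not sized for that outcome.
- A within-arm paired test asks whether HbA1c moved from baseline. Without a placebo arm, a fall in the low-dose arm mixes any drug effect with trial participation and regression to the mean after entry on a high HbA1c. It also says nothing about how 7.5 mg compares with 15 mg.

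If the report concludes that fluid retention was lower and glucose control similar, the second half could rest on a non-significant p-value and an uncontrolled before-after change. Section 3 adds to the difficulty: someone reading it alone would not learn that body fluid is the primary outcome or that glycaemia is unsized.

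**Working it through.** **1. The plan's own figure.** The stated size is 37 per group, 80% power, two-sided 0.05. The effect and SD for body fluid are in figures that are not shown, so 37 cannot be reproduced from its inputs; that is not held against the plan. Back-solving the usual two-means formula gives the standardized difference that 37 per group can detect:

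d = (1.96 + 0.84) × √(2/37) = 2.80 × 0.2325 = 0.65 SD.

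Applied to HbA1c at assumed SDs of change of 0.8 to 1.5 points, this is 0.52 to 0.98 points.

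**2. Precision for HbA1c.** The protocol gives no SD for HbA1c change, so 0.8 to 1.5 points is an assumption. The 0.5-point loss below is also an assumption, used only to illustrate. Unadjusted comparison, 37 per arm, 72 degrees of freedom, t(0.975) = 1.993:

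- Standard error = SD × √(2/37)
- 95% CI half-width = 1.993 × standard error
- Power = two-sided t-test power at noncentrality 0.5 / standard error

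| Assumed SD | Standard error | 95% CI half-width | Noncentrality | Power for a true 0.5-point loss |
| --- | --- | --- | --- | --- |
| 0.8 | 0.186 | 0.37 | 2.69 | 76% |
| 1.0 | 0.232 | 0.46 | 2.15 | 56% |
| 1.2 | 0.279 | 0.56 | 1.79 | 42% |
| 1.5 | 0.349 | 0.70 | 1.43 | 29% |

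A true 0.5-point loss would therefore give p>0.05 in about 24% (100 − 76) to 71% (100 − 29) of such trials.

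**3. What a formal claim of retained efficacy would need.** Non-inferiority with one-sided 0.025, 80% power and a true difference of zero:

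n per arm = 2 × (1.96 + 0.84)² × SD² / margin².

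Across assumed margins of 0.3 to 0.5 points and SDs of 0.8 to 1.5, n runs from 41 (SD 0.8, margin 0.5) to 393 (SD 1.5, margin 0.3). Every case exceeds 37. With 37 per arm the power is 14% to 77% over the same grid (normal approximation).

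**4. The other planned analyses.** ANCOVA and repeated-measures ANOVA with a between-subjects factor are also tests of difference. ANCOVA would supply a suitable estimate, but Section 12 makes it conditional on a baseline difference. In a randomized comparison the reason to adjust for the baseline value is precision, and that reason holds whether or not the baselines look different.

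**The case against.** Five points can be made for the plan.

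- **Sections 3 and 12 do not contradict each other.** A reader might infer from the order of the bullets that glycaemia is primary and that Section 12 overturns it. The text does not support this: Section 3 ranks nothing, and its second bullet covers fluid retention, the domain that Section 12 sizes. What stands is that Section 3 leaves the ranking unsaid.
- **The protocol never claims non-inferiority or equivalence.** This is correct. The aim of keeping the glycaemic benefit is inferred from the title and the rationale, and a difference test on an unsized outcome is an ordinary secondary analysis. The point concerns what those tests can support; it does not allege a false claim in the protocol.
- **Regression to the mean may be limited.** The entry criterion asks for stable treatment with HbA1c above 8% over at least 12 weeks. If that means sustained elevation, regression to the mean is reduced. A participation effect remains possible, and the missing placebo arm is unaffected.
- **A null result is not uninformative at every SD.** A reader might infer that an observed difference of zero could never exclude a 0.5-point loss. That is too strong: at SD 1.0 the half-width is 0.46 and at SD 0.8 it is 0.37, so 0.5 would be excluded. It would not be at SD 1.2 or 1.5. Baseline adjustment could also narrow the interval.
- **Some of this could sit in a SAP.** Reporting conventions often do. Here, though, the protocol itself fixes the primary outcome and the tests, including the condition on ANCOVA and the within-arm tests.

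**Conclusion.** The point holds in a limited form. Body fluid is the only outcome named primary and sized. Glycaemia is an objective of unstated rank, analysed by tests that cannot show that the lower dose keeps its effect. A non-significant between-arm result would be weak evidence of similar control, and a significant within-arm fall would not be comparative evidence at all. The tabulated precision and power rest on 37 analysed per arm, no baseline adjustment and assumed SDs. The comparison of body fluid is not affected.

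**What to change.** - **Section 3:** name change in body fluid as the primary endpoint, matching Section 12, and glycaemic control (HbA1c and fasting glucose) as secondary.
- **Section 12, between arms:** analyse HbA1c and fasting glucose by ANCOVA adjusted for the baseline value in all cases, dropping the condition that baselines differ. Report the between-arm difference with its 95% CI.
- **Section 12, within arms:** show change from baseline descriptively and remove the paired t-tests as tests of efficacy.
- **Interpretation:** state that p>0.05 is not evidence of equal efficacy. Make no non-inferiority claim at this sample size unless a margin is clinically justified and fixed before the data are seen.

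**Cost.** The changes are to wording and analysis only and use data already collected at the planned visits, with no added patients. The downside is a more cautious efficacy statement. A margin-based claim would cost more: it needs a clinical justification that the protocol does not give, and under the assumptions above it needs more than 37 per arm for 80% power.

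### The protocol has the investigator run the randomisation of an open-label, blocked trial and also examine the patients, with no allocation concealment or separation of roles described

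*Protocol*

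**What the plan says.** Protocol section 4 calls the study "A randomized, open-label controlled clinical trial". Method item 4 states that "Subjects will be divided into 2 groups (low and standard dose pioglitazone) by block randomization" and then that "The randomization and drug dispensing will be done by the investigator". Under Method item 7, at every four-weekly visit from week 4 to week 24, "the investigator does the physical examination, symptom and drug adverse event interview, and laboratory testing".

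Section 10, under Subject allocation, adds the mechanics. The ratio is 1:1: "Block randomization divides subjects into low dose group and standard dose group equally". Then: "A randomization in each group is conducted by dividing each subgroup into 20 groups with the setting number 0-19". The numbers are mapped to arms by parity: "The even number group, classified as A, is the intervention group", "And the odd number group, classified as B, is the control group".

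The text at hand does not give the block size, how a patient comes to receive a number, who prepares or keeps the sequence, or how it is hidden from those who enrol. It mentions no central system, sealed envelopes or independent holder.

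**The concern.** Randomisation protects against selection bias only if the person deciding whether and when a patient enters cannot know or guess the next arm. Three features combine against that here. Treatment is open, so past assignments are visible. Allocation is blocked, so past assignments carry information about the next one. And the investigator operates the randomisation, with no stated barrier between the sequence and the people who see patients.

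The consequence is specific to this trial. Section 10 excludes patients with oedema of any origin and those with severe heart disease. Both calls need judgement at the margin. Change in body fluid is the outcome used for the sample size (section 12), and incidence of oedema is part of an objective (section 3). Someone who knows that the higher dose is next could defer a borderline patient, or enrol that patient when the lower dose is due. The arms would then differ at entry on a feature tied to the outcome, and a bioimpedance reading would carry that difference as readily as a clinical judgement.

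Section 12 offers ANCOVA if the arms differ at baseline. That can adjust for what was measured, but not for the impression on which a patient was held back.

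**Working it through.** The protocol states no figure on this point, so there is none to reproduce. The calculation shows how much a blocked, open-label sequence gives away to someone who does not see the list. For someone who does see it, no calculation is needed: the next assignment is known.

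**Inputs.** 1:1 allocation in blocks (sections 4 and 10) and 80 patients (the inflated total in section 12). Block size is not stated, so two sizes are assumed: 20, if the numbers 0 to 19 form one shuffled block, and 4, as a common small block.

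**Guessing rate.** For a block of size 2m with known size and visible past assignments, always guess the arm with more places left. The expected share correct, counting ties as one half, is

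p = [m + (4^m / C(2m, m) − 1) / 2] / (2m)

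- Blocks of 4 (m = 2): [2 + (16/6 − 1)/2] / 4 = 2.833/4 = 0.708.
- Blocks of 20 (m = 10): [10 + (1,048,576/184,756 − 1)/2] / 20 = 12.338/20 = 0.617.

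Simulation of the same rule gave 0.708 and 0.617. Over 80 patients these are about 56.7 and 49.4 correct guesses, against 40 by chance.

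**Assignments known with certainty.** Once one arm of a block is full, the rest are fixed. The expected share is 1/(m + 1): 1/3, or 33%, for blocks of 4; 1/11, or 9%, for blocks of 20.

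**What this could do to a comparison.** Assume enrolment follows the best guess, with the patient's expected outcome shifted by δ standard deviations towards the guessed arm's direction and by nothing when the guess is a tie. With no treatment effect, the expected difference between arms is 2(2p − 1)δ. A two-sided t-test at 5% was simulated with 80 patients and 4,000 runs per setting.

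| Block size | δ (assumed) | Difference by formula | Simulated difference | Simulated type I error |
| --- | --- | --- | --- | --- |
| 4 | 0.25 | 2 × 0.417 × 0.25 = 0.21 | 0.21 | 15% |
| 4 | 0.50 | 2 × 0.417 × 0.50 = 0.42 | 0.42 | 44% |
| 20 | 0.25 | 2 × 0.234 × 0.25 = 0.12 | 0.11 | 8% |
| 20 | 0.50 | 2 × 0.234 × 0.50 = 0.23 | 0.22 | 14% |

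With δ = 0 the simulated error was 5.2% and 4.6%, as it should be. For scale, 37 per group with the 1.96 and 0.84 of section 12 corresponds to a standardised effect of √(2 × 2.80² / 37) = 0.65. This assumes the usual two-mean formula, because the protocol's own formula is in a figure that is not shown.

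The values of δ and the consistent steering are assumptions. The table shows what the gap permits, not what would happen.

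**The case against.** The strongest objection is that the protocol is silent on concealment rather than contrary to it. A list might well be hidden in practice, and the investigator need not be one person. Section 7 provides for a co-investigator, screening is written without an actor, and research staff read the consent form to patients. That is fair as far as it goes: the document does not establish that a single person enrols, allocates and examines. But it assigns allocation and examination to the same role and states nothing that separates them. Nor is this a detail to leave to an analysis plan, since who runs the randomisation is a matter of conduct and the protocol has already decided it.

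Three stronger readings are tempting and should not be drawn.

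- A reader might infer that the even/odd rule makes allocation alternate, or that whole batches of consecutive patients share an arm. The text supports neither. Parity is a labelling code, and it is predictable in itself only if numbers are issued in sequence, which is not said. If numbers are drawn at random and concealed, parity reveals nothing.
- A reader might infer from the order of the Method items that patients are randomised before baseline sampling. The list is not strictly chronological: consent is described after randomisation within item 4, and treatment in item 5 comes before sampling that item 6 places ahead of the first dose.
- A reader might infer that the outcomes at large rest on an unblinded examiner's opinion. Body water, HbA1c, fasting glucose and DEXA results are instrument or laboratory readings. Oedema and reported symptoms are exposed to that judgement, and this assessment bias is a separate question from selection at entry.

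**Conclusion.** The point holds as a defect of concealment and of role separation. As written, the protocol lets the role that examines patients run the sequence of an open-label blocked trial, with no stated safeguard. For anyone with sight of the sequence, foreknowledge can be complete. For someone who knows only block size and history, it is about 62% with a block of 20 and 71% with blocks of 4, against 50% by chance. Those rates depend on assumed block sizes. The error rates of 8% to 44% depend further on assumed, deliberate steering of enrolment and should not be read as forecasts.

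The conclusion does not rest on the parity rule, on one person filling every role, or on any particular block size. It rests on what sections 4 and 10 assign and leave unprotected, in a trial where a judgement-based exclusion is closely related to the fluid outcomes. It deserves correction before enrolment because the resulting bias could not be fully removed afterwards and prevention is cheap.

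**What to change.** Amend Method item 4 in section 4 and Subject allocation in section 10 as follows.

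- Use a computer-generated 1:1 permuted-block list with randomly varying block sizes that are not disclosed to those who enrol.
- Have it prepared and held by an existing person who does not consent, enrol or examine patients. The hospital pharmacy would serve if it is available, which the protocol does not say. Research staff who take consent should not hold it.
- Release each assignment from a sequentially numbered, opaque, sealed envelope, opened only after consent, eligibility and baseline measurements are recorded.
- Let the list take the place of the 0 to 19 numbering. A and B may stay as arm labels.

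Open-label treatment can continue, and no patients or visits are added. The costs are a small administrative burden and reliance on finding an independent list holder at the site.

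### Section 10 plans for 74 subjects with no allowance for loss, while Section 12 plans for 80 after a 10% allowance; 74 does not support the stated 80% power

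*Protocol*

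**What the plan says.** Section 10 (study population) opens with "Expected number of subjects: 74 subjects" and then lists eligibility, withdrawal criteria and allocation. It does not describe the 74 as completers or as evaluable subjects. Allocation is 1:1: "Block randomization divides subjects into low dose group and standard dose group equally".

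Section 12 (statistical justification) ties the power claim to 37 per group: "The target sample size was 37 subjects per group that will provide 80% power to detect a significant effect", at a two-sided 5% level, with change in body fluid as the primary outcome. It repeats the result ("By the calculation, the quantity of subject per group is 37") and then adds an allowance: "But with the follow up, the 10% loss follow up of the calculated number is considered". Its conclusion is "Therefore, the quantity of subject per group is 40, total is 80".

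**The concern.** A protocol should carry one enrolment target. Here the section that describes the study population gives 74, and the section that justifies the sample size gives 80. Since 74 = 2 x 37, Section 10 appears to have taken the calculated number and left out the step that Section 12 then treats as necessary.

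A team that follows Section 10 would stop six subjects early, with nothing in reserve for the loss the plan itself expects. The 80% power for body fluid is the only operating characteristic the protocol states, so the choice between the two numbers decides whether that figure is roughly met or missed by several points.

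**Working it through.** **Inputs.** From Section 12: two-sided alpha 0.05 (z = 1.96), power 80% (z = 0.84), 37 per group calculated, 10% loss, 40 per group and 80 in total after the allowance. From Section 10: 74 subjects, allocated 1:1.

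**Not available.** The effect and SD stand in figures not shown, so the 37 itself cannot be checked.

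**Step 1: the plan's 40.** Section 12 takes 10% of the calculated number: 37 x 1.10 = 40.7. Cutting off the decimal gives the stated 40, and 2 x 40 = 80. Rounding up would give 41. Dividing by the expected retention instead gives 37/0.9 = 41.1, rounded up to 42.

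**Step 2: the 74.** 2 x 37 = 74, so Section 10 contains no allowance.

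**Step 3: evaluable subjects after 10% loss.**
- 74 enrolled: 37 x 0.9 = 33.3, so about 33 per arm.
- 80 enrolled: 40 x 0.9 = 36 per arm.

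**Step 4: implied effect (an assumption).** For two equal groups, n = 2(1.96 + 0.84)²/d², so d = 2.80 x sqrt(2/n). An unrounded n of exactly 37 gives d = 0.651. An unrounded n just above 36, rounded up to 37, gives d = 0.660. Every d in this range leads to 37 per group when n is rounded up.

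**Step 5: power.** Normal formula: power = Φ(d x sqrt(n/2) − 1.96). At n = 33 and d = 0.651, 0.651 x sqrt(16.5) − 1.96 = 0.684, so power is 75.3%. The t-test column uses the noncentral t distribution with 2n − 2 degrees of freedom. In each range the first figure is for d = 0.651 and the second for d = 0.660.

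| Evaluable per arm | How it arises | Normal formula | t-test |
|---|---|---|---|
| 37 | 74 enrolled, nobody lost | 80.0% to 81.1% | 78.9% to 80.0% |
| 36 | 80 enrolled, 10% lost | 78.9% to 80.0% | 77.8% to 78.9% |
| 33 | 74 enrolled, 10% lost | 75.3% to 76.5% | 74.0% to 75.2% |

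With the method and the effect held fixed, going from 37 to 33 per arm costs between 4.6 and 4.9 points, and going from 37 to 36 costs about 1 point.

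**The case against.** The strongest reply is that Section 12 shows where both numbers come from, so a careful reader can see that 74 is the figure before the allowance and 80 the figure after it. That is fair, and it means the protocol does not leave a site wholly without guidance on when to stop. It does not remove the contradiction: Section 10 offers 74 as the expected number of subjects without qualification, and nothing says which section governs.

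It could also be said that the planned analysis fills missing values with the group mean, so that all randomised subjects are counted. Filling in a mean adds no information, so this does not bring back the power lost with the subjects.

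Three stronger readings are tempting, and the document does not support them.

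- **A reader might infer that neither total delivers the stated power.** It is true that neither leaves 37 per arm. At 80 enrolled, however, the gap is one subject per arm, and power on the plan's formula is 78.9% to 80.0%. A figure of 77.8% at 36 per arm comes from deriving the effect with the normal formula, taking its lowest value, and then computing power by t-test. On that basis even 37 per arm with nobody lost gives only 78.9%, so about half of the apparent shortfall is due to the change of method.
- **A reader might infer that 84 is the correct total.** That follows from dividing by 0.9. Section 12 instead describes its allowance as "the 10% loss follow up of the calculated number is considered", which gives 40.7. By the plan's own rule the only slip is cutting 40.7 to 40 rather than rounding up to 41.
- **A reader might infer that loss will exceed 10%**, because the withdrawal criteria include heart failure, volume overload and other events. The protocol gives no rate for these, so no size can be put on it.

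**Conclusion.** The contradiction between 74 and 80 is real and visible on the face of the protocol. It matters in one direction. Enrolling 74 under the plan's own 10% loss leaves the trial about 3.5 to 4.7 points below the stated 80% on the plan's formula, and 4.8 to 6.0 points below it by t-test. Enrolling 80 comes within about 1 point of 80% on the plan's formula, which is a matter of rounding.

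The power figures rest on the effect implied by 37 per group, on the assumption that the calculated value was rounded up to 37. Had it been rounded down, all of them would be somewhat lower. The contradiction itself, and the counts of 33 and 36 per arm, do not depend on any assumed effect.

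**What to change.** Change the expected number in Section 10 from 74 to 80 (40 per group), so that it agrees with Section 12.

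In Section 12, add that about 36 per arm are expected to be evaluable after 10% loss. State the power at that number: about 79% to 80% on the plan's formula, and about 1 point lower by t-test. The sponsor holds the effect and SD behind the 37, so it can replace the range with one figure and name the method used. No larger enrolment is needed.

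The cost is wording in two sections and a stated power up to about 1 point lower on the plan's formula, or about 2 points lower if the t-test figure is quoted.
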